### Ethical considerations

All local ethical committees of the participating hospitals (Ethical Review Commission Jessaziekenhuis; Committee Medical Ethics Ziekenhuis Oost-Limburg; Ethical Committee AZ Vesalius; Ethical Committee Mariaziekenhuis Noord-Limburg) and the university (Medical Ethical Committee Hasselt University) reviewed all study materials including: the recruitment materials and procedure, informed consent form, the questionnaires and the overall study protocol. The leading ethical committee (ERC Jessaziekenhuis) coordinated the process, collected feedback and granted approval on 26^th^ of February 2014 (BE24320149544). The leading ethical committee also reviewed and approved study protocol amendments.

### Data analysis

The Statistical Package for Social Sciences (SPSS; Chicago, IL) version 22.0 will be used for statistical analyses of the quantitative data. A range of analyses are required to report the reliability and validity of the translated CARES version.

### Reliability

The reliability of the CARES will be evaluated by computing the *internal consistency* of summary scales, with the aim to find a Cohen’s Alpha of at least .70 [71, 72]. *Test-retest reliability* will be investigated by computing the intra-class correlations between the summary scale scores and total-CARES scores of the first and second CARES administration, requiring a correlation ≥ .70 [71, 73].

### Construct validity

The five factor structure as found in previous CARES-research will be examined with principal component analysis to evaluate construct validity. Following previous validation techniques applied in the original CARES development process, items and subscales with a factor loading higher as .30 are seen as loading on a factor [34, 35]. Confirmatory factor analysis will not be applied since sample size will be limited. As well inter-correlations of summary scales and the CARES Total will be explored. Moderate correlations between the subscales (*r* = |.30|-|.70|) and moderate to high correlations with the CARES Total (*r* ≥ .30) would support construct validity, since this would indicate that the subscales indeed measure distinct, but related concepts that contribute to the larger concept of QOL.

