*Abbreviations*: CaNDI (Cancer Needs Distress Inventory), CARES (Cancer Rehabilitation Evaluation System), CARES-SF (Cancer Rehabilitation Evaluation System-Short Form), CCM (Cancer care monitor), CHOICEs assessment (Creating better health outcomes by improving communication about patients’ experiences assessment), CNAT (Comprehensive needs assessment tool in cancer), CNQ-SF (Cancer Needs Questionnaire Short Form), CPILS (Cancer Problems in Living Scale), CPNS (Cancer Patient Need Survey) CPNQ (Cancer Patient Need Questionnaire), Distress management tool, INM (Information Needs Measure), NEQ (Need Evaluation Questionnaire), OCPC (Oncology Clinic Patient Checklist), PINQ (Patient Information Need Questionnaire), PNAS (Psychosocial needs assessment survey), PNAT (Patient Needs Assessment Tool), PNI (Psychosocial Needs Inventory), Problem checklist, SCNS (Supportive Care Needs Survey), SCNS-SF34 (Supportive Care Needs Survey Short Form), SNST (Supportive Care Needs screening Tool), Symptoms and concerns checklist

Among other tools, the Cancer Rehabilitation Evaluation System (CARES) was positively evaluated [28–30]. The CARES is a QOL and needs assessment instrument, developed to provide an efficient way of gathering specific information about the day-to-day problems and rehabilitation needs of cancer patients. The instrument can be used for research or clinical objectives and has been applied across cancer type and stage [31–44]. The 139 items of the CARES are placed under 31 subscales and represented according to six summary scales, as shown in Table 2. A copy of the original CARES questionnaire and patient score profile can be found in Additional files 2 and 3.

**Table 2 Tab2:** CARES Summary scales and subscales

Summary scales (n items)	Subscales
Physical (26)	Ambulation Activities of daily living Recreational activities Weight loss Difficulty working Pain Clothing
Medical Interaction (11)	Problems obtaining info from medical team Difficulty communicating with medical team Control of medical team
Marital^a^ (18)	Communication with partner Affection with partner Interaction with partner Overprotection by partner Neglect of care by partner
Psychosocial (44)	Body image Psychological distress Cognitive problems Difficulty communicating with friends/relatives Friends/relatives difficulty interacting Anxiety in medical situations Worry Interaction with children^a^ At work concerns^a^
Sexual (8)	Sex interest Sexual dysfunction^a^

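### The r ≥ .30 rule for a scale's correlation with the CARES Total includes the scale's own items, so it is not independent evidence of construct validity

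*Protocol article*

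**What the plan says.** Under Construct validity, the article first plans a principal component analysis of the five-factor structure, with loadings above .30 counted. It then says that "inter-correlations of summary scales and the CARES Total will be explored". Two conditions are joined by 'and': "Moderate correlations between the subscales", set at .30 to .70 in absolute value, and "moderate to high correlations with the CARES Total", set at r ≥ .30. Meeting them is taken to show that "the subscales indeed measure distinct, but related concepts that contribute to the larger concept of QOL". The sentence says subscales where the planned correlations are between summary scales; I read both as summary scales.

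The scales and the Total come from one item pool. The Background states: "The 139 items of the CARES are placed under 31 subscales and represented according to six summary scales". Table 2 gives the item counts. The CARES paragraph under Questionnaires says that five summary scales and a global score can be computed, without a scoring formula. Nothing says that a scale's own items are removed from the Total before the two are correlated.

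**The concern.** A correlation between a part and a whole that contains it is inflated by the part's own variance. Scale lengths run from 8 to 44 items, so the inflation is large and unequal. A single cut-off of .30 then asks much less of the longest scale than of the shortest, and a pass partly reflects length rather than any relation to the rest of the instrument.

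A column of Total correlations between .4 and .8 would read as corroboration of the Flemish version. The article says a version found reliable, valid and feasible will go into research and clinical practice. If part of that column is arithmetic, readers should be able to see how much.

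A smaller point concerns sign. The inter-scale band is stated in absolute values, yet all CARES items are problem statements scored from 0 (no problem) to 4 (severe problem). A clearly negative correlation between two scales would count against a shared construct, but it meets the rule as written.

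**Working it through.** The cut-off of .30 is a convention, so there is no derived figure to reproduce.

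**Inputs.** Table 2 gives Physical 26, Medical Interaction 11, Marital 18, Psychosocial 44, Sexual 8 and Miscellaneous 32 items. These sum to 139, as stated. The first five sum to 107. I ran the Total with five blocks and with six (adding Miscellaneous), because the article does not say which applies.

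**Assumptions.** The Total is a sum of items, item variances are equal, and the mean inter-item correlation r is .25 to .40 within every scale. The documents do not give r. As a second setting I used a common alpha of .87 to .94, the range the Background reports for the original CARES, converted by r = α / (k − α(k − 1)).

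**Formulas.** The variance of a scale with k items is V = k[1 + (k − 1)r]. If the scales are mutually uncorrelated, the correlation of scale j with the Total is √(V_j / ΣV).

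**Example at r = .25.** Physical: V = 26 × 7.25 = 188.5. Psychosocial: V = 44 × 11.75 = 517. ΣV is 860.5 for five blocks and 1140.5 for six.
- Physical: √(188.5/860.5) = .47; √(188.5/1140.5) = .41.
- Psychosocial: √(517/860.5) = .78; √(517/1140.5) = .67.

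**Correlation with the Total when the true inter-scale correlation is 0 (five or six blocks):**

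| Scale | Items | Inter-item r .25–.40 | Common alpha .87–.94 |
|---|---|---|---|
| Psychosocial | 44 | .67–.78 | .59–.70 |
| Physical | 26 | .41–.47 | .43–.50 |
| Marital | 18 | .28–.33 | .33–.40 |
| Medical Interaction | 11 | .18–.21 | .23–.29 |
| Sexual | 8 | .13–.16 | .18–.23 |

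If scales are weighted equally instead, every value is 1/√5 = .45 or 1/√6 = .41. With a scale's own items removed, every value is 0.

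**Common true inter-scale correlation c, inter-item r .25–.40:**

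| c | Lowest uncorrected value | Corrected values |
|---|---|---|
| .10 | .29 | .15–.18 |
| .15 | .35 | .22–.25 |
| .20 | .41 | .29–.32 |
| .30 | .51 | .40–.44 |

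At c = .15, half the plan's own inter-scale floor, every scale passes uncorrected and none passes corrected. The corrected value reaches .30 at c of about .20.

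**A mixed pattern.** Let Physical correlate .10 with every other scale while the others correlate .40 with each other (r = .25, six blocks). The SD of Physical is √188.5 = 13.73. The SDs of the other five sum to 60.09 and their variances to 952. The variance of the rest is .6 × 952 + .4 × 60.09² ≈ 2015, so its SD is 44.9.
- Corrected: .10 × 60.09 / 44.9 = .13.
- Uncorrected: (13.73 + 6.01) / √(188.5 + 2015 + 2 × .10 × 13.73 × 60.09) = 19.74 / 48.67 = .41.

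With five blocks the values are .13 and .47. Physical fails the inter-scale band with every other scale and still passes the Total condition.

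**The inter-scale condition on unrelated scales.** In 10,000 simulated samples of 150, at least one pair reached an absolute correlation of .30 in about 0.2–0.3% of runs, and all pairs did so in none.

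**The case against.** The strongest reply is that the Total condition does not stand alone. A reader might infer that essentially unrelated scales could be declared construct-valid. The documents do not support that: the two conditions are joined by 'and', the inter-scale condition has no overlap problem, and unrelated scales fail it. Principal component analysis is also run, and the correlations are described as explored. This stands.

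Nor does the condition pass automatically for every scale. With an item-sum Total, Sexual never passes on overlap alone under any assumption tried. Medical Interaction does so only in two five-block settings: uncorrelated items (.32) and a common alpha of .70 (.31). All scales pass together on overlap alone only with equal weighting, which the article does not state. This stands too, and the exact sizes depend on an unstated formula.

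It can also be said that the correction rarely changes the joint result. Where every pair reaches .30, the corrected values are about .40–.44 and pass as well. That is right, but it also means the uncorrected condition (.51 or more there) cannot fail when the first is met. The article gives no rule for weak or mixed inter-scale results, and there the two versions diverge.

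On sign, five scales cannot all correlate with each other below −.25 (−1/(5 − 1)), so a uniformly negative pattern in the band is impossible, and the Total condition is already signed. Only single negative pairs are at issue, which keeps this point minor.

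**Conclusion.** The concern holds in a limited form. The Total condition is not independent evidence of construct validity. For the two longest scored scales, Psychosocial and Physical, overlap alone exceeds .30 under every assumption tried. For Marital it depends on the assumption, and for the two shortest scales it generally falls short. When all inter-scale correlations reach .30 the condition is redundant. When they are weak or mixed it can endorse a scale that is barely related to the rest, for example .41–.47 uncorrected against .13 corrected for Physical. It does not by itself let unrelated scales satisfy the full criterion.

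The sizes rest on a Total that sums the scales' items, equal item variances and the stated ranges for inter-item correlation or alpha. Items that do not apply to every patient, including the Marital scale, would change the weights. The mechanism depends only on the Total containing the scale.

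**What to change.** Correlate each summary scale with the CARES Total minus that scale's own items, and apply r ≥ .30 to this corrected value. State the formula for the Total, including whether the Miscellaneous items enter. If the uncorrected coefficients are kept for comparison with the original CARES, report them beside the corrected ones and attach no criterion to them.

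As a secondary change, state the inter-scale band as positive, +.30 to +.70, in line with the signs that Table 5 already sets for the concurrent instruments.

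The cost is one computed variable per scale from data already planned, and smaller reported coefficients. No further patients or questionnaires are needed.

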### Concurrent validity

Spearmans rank correlations will be computed to evaluate concurrent validity of the CARES global score and the summary scales with the seven concurrent instruments (Table 5). Correlations will be judged low, moderate and high, when their absolute values are respectively < .30, from .30 to .50 and ≥ .50 [74].

If the psychometric qualities do not show as expected, these will be studied in more detail with qualitative research data on CARES content and feasibility to search for explanations.

## Discussion

To achieve good quality care it is important to provide it as efficiently as possible, and adapted to the individual needs of every patient. A stepped care approach according to patients’ level of need could serve to tailor care efficiently and appropriately, however this necessitates reliable and valid screening and assessment tools to support clinicians in the identification of psychosocial concerns and care needs of their patients. The current English CARES is such an instrument. This paper describes a comprehensive protocol for translating and validating a Flemish CARES version. This addresses a critical gap in current clinical screening, and adds a tool to assess and improve the delivery of patient-centered care.

Unique in this study is the use of a wide range of comparative instruments to examine the concurrent validity of the CARES. Many other validation studies use only a few dimensions, not reflecting the whole concept of the specific instrument [28, 29, 75]. In contrast, this study will include an instrument to examine concurrent validity almost for each summary scale and the CARES global score. While our study is set up to examine the psychometric quality of the Flemish CARES, an additional advantage is that the use of several concurrent instruments will provide us with a wealth of data. The use of the KPS, HADS, SSL, MMQ, EORTC QLQ-C30, DT, PL and the Care needs questionnaire of Pauwels et. al. provides data on psychological, social, marital and sexual wellbeing, QOL, distress and care needs of patients treated for cancer. These can be used to explore potential relationships between mutual care-domains and with socio-demographic and medical characteristics. The recruitment for this study has begun (March 2014) and will continue until the end of 2014 or until the desired sample size is reached.

As in all studies, this study has some limitations. Firstly, the completeness of the CARES content to assess QOL and supportive care needs should be considered. In comparison to other psychometric positively evaluated needs assessment tools for cancer patients, like the Supportive Care Needs Survey (SCNS) [76], the CARES does not include items on spiritual and existential well-being [29]. However, on other domains of well-being, we can judge in favor of the CARES content. The content of the CARES matches with our thoughts about the bio-psychosocial impact of cancer on patients’ lives and possibly resulting care needs. Furthermore, the content validity, completeness and feasibility of the CARES for Flemish cancer patients will be explored in the qualitative part of the larger study combining qualitative and quantitative methods. If the results of the study described in this research protocol result in a negative evaluation of the CARES’ psychometric properties, or it appears from the focus group discussions that there are deficits in the CARES content, formulation of items, or feasibility, adjustments for an improved Flemish version will be made. We plan to use this ‘final’ Flemish version in a pilot study where it will support the routine assessment and management of patients’ psychosocial concerns and needs in a clinical pathway with medical and psychosocial components. In the future, the instrument will also be made available for use in clinical practice.

Secondly, the use of two procedures to invite patients to participate in the study can introduce bias. An invitation to participate in research from a member of the medical team or by post could result in different response rates in both subgroups. This is a demanding study for patients and therefore also for professionals to convince patients to participate. Hence, some flexibility in the process of patient recruitment is needed. Some departments prefer a personal approach and want to invite their patients for the research personally, while others do not find the time in the clinical appointment to do this. Both procedures have been previously used in other validation research [66, 75, 77–80]. To assess any recruitment or consent bias, we will compare the data from the group of patients invited to participate in the hospital to the group invited by post.

Thirdly, the questionnaire package composed with the CARES and several concurrent instruments asks for a time-investment of approximately an hour. This could present a burden to participants, resulting in discontinuation of participation. However, preliminary study results report approximately 58 % of the questionnaires distributed were returned completed. Eighty-four percent of the 153 participants who returned the first questionnaire also returned the second questionnaire completed.

Fourthly, the time between completing of the first and the second CARES survey could pose some problems. To examine test-retest reliability of an instrument the time period between two completions should be short enough to ensure that clinical change has not occurred, though long enough to prevent recall. While 1 or 2 weeks are recommended in literature [53], we ask participants to fill out the second questionnaire 1 week after the first. Preliminary results have shown some participants forget to fill in the second questionnaire or do not do so in a timely manner. They are reminded with a phone call by the researcher when de second questionnaire is not received in the recommended period of time. When data collection is completed, the time span between the two CARES-completions will be evaluated.

Fifthly, in earlier research the CARES was validated and used as a research tool for participants with various types of cancers, various cancer stages, at different phases of the care process, and often without age restrictions [31–44]. Because of the strict inclusion criteria we applied in our study, we have to state that the validation evidence from this study will not apply to patients above 60 years of age, and those with metastatic disease or in palliative care.”

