### Study procedure

Eligible patients will be selected by the medical team according to the inclusion and exclusion criteria. Given the complexity of the clinical field and variable structures of the participating departments, two alternative procedures to invite patients to participate in the study will be used. On the basis of team organization and availability of time, the physician of the medical unit will choose to recruit patients with either the ‘face-to-face procedure’ or the ‘post procedure’. In the ‘face-to-face procedure’, a member of the medical team will explain the study briefly and invite the patient to participate. If the patient agrees to participate, he/she will immediately receive a study package with the informed consent form, a ‘what to do’-scheme, the first questionnaire and a stamped and addressed envelope to return the questionnaire. In the ‘post procedure’, eligible patients will be sent an identical study package by post, containing a short letter explaining the study, the informed consent form, a ‘what to do’-scheme, the first questionnaire and a stamped and addressed envelope to return the questionnaire. One week later participants have to fill in the second questionnaire, containing the CARES for test-retest reliability, and send it back in another stamped and addressed envelope provided. If the questionnaire is not sent back, the participants recruited via the ‘face-to-face procedures will be contacted by a team member and asked if they still want to participate and asked to return a completed questionnaire. Participants invited through post-procedure will be sent a reminder and second questionnaire package after 1 month. This study procedure is visualized in Fig. 1.

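### The hospital-versus-post comparison can show only bias that differs between invitation routes, not any consent bias, and unadjusted it is confounded with department and case mix

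*Protocol article*

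**What the plan says.** The second limitation in the Discussion of the protocol article concedes that "the use of two procedures to invite patients to participate in the study can introduce bias". It expects this to happen because the two forms of invitation "could result in different response rates in both subgroups". The remedy follows at the end of the same paragraph: "To assess any recruitment or consent bias, we will compare the data from the group of patients invited to participate in the hospital" with those invited by post. No adjustment is mentioned.

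The Study procedure section explains how a patient comes to be in one group or the other: "On the basis of team organization and availability of time", "the physician of the medical unit will choose to recruit patients with either the" the face-to-face or the postal procedure. The Discussion adds that departments differ in which they prefer.

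The two routes also differ in when the package is given. Face to face, the invitation comes first: "If the patient agrees to participate, he/she will immediately receive a study package". By post, every eligible patient selected for that route is sent the package unasked. Follow-up of non-return differs too: contact by a team member in one route, and a mailed reminder with a further package after a month in the other.

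**The concern.** Consent bias is a difference between those who take part and those who do not. The planned check sets participants against participants. If patients with heavier needs, or with lighter ones, decline to the same degree under both routes, the two groups look alike however large the bias is. The stated aim, which covers any recruitment or consent bias, is therefore wider than the comparison can serve.

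The second problem is attribution. Because route is chosen at unit level, hospital versus post is partly one set of departments against another. An observed difference may be case mix, and an observed similarity may be a route effect cancelled by case mix.

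What is at stake is how the result is read. A null finding could be taken as evidence that consent bias is absent, and a difference as evidence that the manner of invitation caused it. Neither conclusion would follow from the comparison as written.

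**Working it through.** The article attaches no sample size, effect size or error rate to this check, so there is no figure of its own to reproduce. The argument rests first on setting the sections side by side.

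**What the article fixes**
- Patient data, including socio-demographic and medical characteristics, come from the first questionnaire (Questionnaires section, Table 6). They exist for those who return it. No comparison with decliners or non-returners is described.
- Route is chosen by the unit physician (Study procedure).
- Recruiting departments are medical oncology, radiotherapy, gynecology, urology and gastroenterology, in four hospitals (Study population and recruitment). Their case mix can be expected to differ.
- Diagnosis, date of diagnosis, treatments and treatment dates are collected (Table 6).

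**Illustration of size (assumed values, not document figures)**

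Let a need score Y be standard normal among invited patients, and let the probability of responding be p(Y) = 1/(1 + exp(−(a + bY))), with a set to give the chosen response rate. The respondents' mean is E[pY]/E[p], and its distance from 0 is the consent bias. Take the target of 150 split as 75 per route. The standard error of the route difference is √(1/75 + 1/75) = 0.163 SD, and the chance of a two-sided 5% result is approximately Φ(|d|/0.163 − 1.96) when d is well away from 0.

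1. *Same selection, same response (58%) in both routes.* With b = −0.5 both means are −0.20 SD; with b = −1 both are −0.35 SD. The route difference is 0 and the chance of a significant result is 5%, the false-positive rate.
2. *Same selection, response 60% versus 40%.* With b = −0.5 the biases are −0.19 and −0.28 SD (before rounding, −0.189 and −0.284), a difference of 0.095 SD that is detected 9% of the time. With b = −1 they are −0.33 and −0.50 SD (−0.332 and −0.498), a difference of 0.166 SD, detected 17% of the time.
3. *Selection in one route only, 58% response.* The difference equals the bias. For 0.20 SD the power is 23%; for 0.35 SD it is 57%. Bias of this kind can be seen, though weakly.
4. *No consent bias, departments 0.5 SD apart.* If route and department coincide, d = 0.5; 0.5/0.163 = 3.06, and Φ(3.06 − 1.96) = 87%. If the higher-need departments supply 80% of one route and 20% of the other, d = 0.5 × (0.8 − 0.2) = 0.30; 0.30/0.163 = 1.84, and Φ(1.84 − 1.96) = 45%. Both are false alarms.
5. *Masking.* If the route that receives more of the higher-need departments (+0.30 SD, as in item 4) also carries a consent bias of −0.35 SD, the observed difference is about −0.35 + 0.30 = −0.05 SD.

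The difference detectable with 80% power is (1.96 + 0.84) × √(1/n₁ + 1/n₂): 0.46 SD for 75/75, 0.49 for 50/100 and 0.57 for 30/120. The actual split is not stated.

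**Response per patient invited**

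For the postal route this equals the return rate. For the face-to-face route it is (1 − proportion refusing at invitation) × return rate. Anyone examining the mechanism that the Discussion names would need the first factor, and a count of packages does not supply it.

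**The case against.** The paragraph is about bias from using two procedures, and comparing the two procedures is the natural check for that. This stands. A reader might infer that the check cannot detect consent bias at all, or that it is bound to reassure falsely. The article supports neither reading: bias that differs by route is detectable (item 3), and confounding with department can raise an alarm as readily as suppress one (items 4 and 5). Only the breadth of the stated aim overreaches.

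Confounding may also be partial. The number of units using each route is not given, and with four hospitals the same specialty may appear under both. This stands too, and is why the 87% and 45% are illustrations, not estimates.

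The article plans no comparison of return rates per package. The 58% "of the questionnaires distributed were returned completed" is a pooled preliminary figure, cited in connection with participant burden. It is tempting to divide 153 by 0.58, obtain about 264 packages, and conclude that some 111 people are unseen by the check. The text does not support that: it does not say that the 58% and the 153 describe the same batch, and postal non-returners are sent another package, so packages may outnumber people. Nor does the aim of a representative sample rest on this check; the article rests it on recruiting through several departments.

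Finally, an article may leave covariates and recruitment counts to fuller documents. That disposes of any complaint about missing detail. It does not dispose of an aim stated more widely than the stated comparison can reach.

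**Conclusion.** The concern holds in a limited form. Two points follow from the article alone, without the illustration: selection common to both routes is invisible to a comparison of respondents, and a route chosen by unit is tied to department and hence to case mix. The numerical sizes rest on the assumed selection slopes, case-mix difference and route split. They show only that the check could miss consent bias of 0.20 to 0.35 SD and could flag a case-mix difference as bias.

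The importance is modest. The article's main analyses are internal consistency, test-retest agreement, principal components and concurrent correlations, and no change to any of these has been shown. What is affected is mainly generalisability and the descriptive picture of patients' needs. The correction is still worth making, because the result could be misread in either direction and most of the data needed for a better comparison are already being collected.

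**What to change.** 1. Restate the aim: the comparison assesses differences between invitation routes only. State that a null result will not be interpreted as absence of consent bias.
2. Compare routes within, or adjusted for, department or hospital, diagnosis, treatment phase and time since diagnosis. Diagnosis, its date and the treatment dates are in Table 6. Recruiting unit is not listed there and is assumed to be known from study administration. Describe any remaining difference as belonging to the route as a whole, follow-up included.
3. Where unit records allow, report by route the numbers approached, agreed and returned, with response expressed per patient invited.
4. Optionally, add aggregate characteristics of non-participants, if they are available and the ethics committees permit it.

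The cost is a little more analysis, some loss of precision after adjustment, and a narrower claim. Recruitment began in March 2014 and 153 first questionnaires are already back, so past face-to-face refusals may not be recoverable; if so, the report should say so.
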